## Abstract

**Background:**

Most quality improvement programs in diabetes care incorporate aspects of clinician education, performance feedback, patient education, care management, and diabetes care teams to support primary care physicians. Few studies have applied all of these dimensions to address clinical inertia.

**Aim:**

To evaluate interventions to improve adherence to evidence-based guidelines for diabetes and reduce clinical inertia in primary care physicians.

**Design:**

Two-arm cluster randomized controlled trial.

**Participants:**

Primary care physicians in Belgium.

**Interventions:**

Primary care physicians will be randomly allocated to 'Usual' (UQIP) or 'Advanced' (AQIP) Quality Improvement Programs. Physicians in the UQIP will receive interventions addressing the main physician, patient, and office system factors that contribute to clinical inertia. Physicians in the AQIP will receive additional interventions that focus on sustainable behavior changes in patients and providers.

**Outcomes:**

Primary endpoints are the proportions of patients within targets for three clinical outcomes: 1) glycosylated hemoglobin < 7%; 2) systolic blood pressure differences ≤130 mmHg; and 3) low density lipoprotein/cholesterol < 100 mg/dl. Secondary endpoints are individual improvements in 12 validated parameters: glycosylated hemoglobin, low and high density lipoprotein/cholesterol, total cholesterol, systolic blood pressure, diastolic blood pressure, weight, physical exercise, healthy diet, smoking status, and statin and anti-platelet therapy.

**Primary and secondary analysis:**

Statistical analyses will be performed using an intent-to-treat approach with a multilevel model. Linear and generalized linear mixed models will be used to account for the clustered nature of the data, *i.e*., patients clustered withinimary care physicians, and repeated assessments clustered within patients. To compare patient characteristics at baseline and between the intervention arms, the generalized estimating equations (GEE) approach will be used, taking the clustered nature of the data within physicians into account. We will also use the GEE approach to test for differences in evolution of the primary and secondary endpoints for all patients, and for patients in the two interventions arms, accounting for within-patient clustering.

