## Methods

### Study design

The study is an open pragmatic cluster randomized trial with before/after measurements and two intervention arms. A cluster design is necessary because randomization is performed on a practice level, the intervention happens on the physician level, but a large part of the data are analyzed at the patient level. The implementation period of the trial is 18 months.

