### Sample size

The project funding agency requires a sample size of at least one-third of the potential PCPs (n = 379), which would capture roughly 2,500 patients with type 2 diabetes mellitus. This sample size allows 80% power (type II error: 0.20) to detect a 20% relative difference between the intervention arms in the proportion of patients achieving a 10% improvement in any one of the following: blood pressure, total cholesterol, or HbA1c (type I error: 0.05; assumed intracluster coefficient 0.6; [67] for calculation methods).

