### Statistical analysis

Statistical analyses will be performed using an intent-to-treat approach with a multilevel model. Linear and generalized linear mixed models will be used to account for the clustered nature of the data, *i.e*., patients clustered within PCPs, and repeated assessments clustered within patients. Such models measure how outcomes change over time within patients and whether these changes depend on patient and/or PCP's characteristics, such as the intervention program or DCT use (see hypothesis two). DCT use is defined as having at least one consultation with a member of the team besides the health psychologist and the traveling educator, which are only available for AQIP patients.

We will use generalized estimating equations (GEE), an extension of the quasi-likelihood approach, to test for differences in the evolution of the primary and secondary endpoints for all patients and within the intervention arms. For binary variables, we use the exponential inverse transformation to obtain the 95% confidence interval for the odds ratio.

Subgroup analyses (see hypothesis one) can distinguish intervention effects using different cut-off values. For HbA1C, three subgroups are defined: patients with HbA1c < 7%; HbA1c ≥ 7% and < 8%; and HbA1c ≥ 8%. For SBP, four subgroups are defined: patients with SBP ≤ 130 mmHg; SBP > 130 mmHg and ≤ 140 mmHg; SBP > 140 mmHg and ≤ 160 mmHg; and SBP > 160 mmHg. For LDL-C, four subgroups are defined: patients with LDL-C < 100 mg/dl; LDL-C ≥ 100 mg/dl and < 115 mg/dl; LDL-C ≥ 115 mg/dl and < 130 mg/dl; and LDL-C > 130 mg/dl.

Linear mixed models with subject-specific intercepts and slopes are used to test whether subject-specific evolutions are related to initial parameters. HbA1c will be transformed logarithmically to meet the parametric assumptions of the statistical models. All analyses will be performed using SAS, version 9.

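### The endpoint GEE is specified with within-patient clustering, which omits the randomised practice; its standard errors are too small if change over time is correlated within physicians or practices

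*Protocol article*

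**What the plan says.** The protocol article describes three uses of clustered models.

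- **Mixed models** (abstract, Primary and secondary analysis; Methods, Statistical analysis). These have "patients clustered within PCPs, and repeated assessments clustered within patients". The Methods use them to examine how outcomes change and "whether these changes depend on patient and/or PCP's characteristics, such as the intervention program or DCT use".
- **GEE for the baseline comparison** (abstract only), described as "taking the clustered nature of the data within physicians into account".
- **GEE for the endpoints.** The abstract applies it to the evolution of the primary and secondary endpoints "for all patients, and for patients in the two interventions arms, accounting for within-patient clustering". The Methods apply it "to test for differences in the evolution of the primary and secondary endpoints for all patients and within the intervention arms" and name no clustering level. The sentence that follows in the Methods describes the 95% confidence interval for the odds ratio of binary variables.

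Under Study design the article states that "randomization is performed on a practice level, the intervention happens on the physician level". The Background and the section on randomization also give the practice as the unit allocated, and the strata include duo and group practices.

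**The concern.** Two consecutive sentences of the abstract use the same method with different clusters: the physician for baseline characteristics, then the patient for the endpoints. Patients are nested in practices and share an allocation. If the patient is the independent unit of the GEE, patients of one physician are treated as independent of each other, and the robust variance cannot pick up any correlation between them. The Methods do not correct this.

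The primary endpoints are proportions. Because the odds-ratio interval is described directly after the GEE, a natural reading is that the intervals for the primary endpoints come from the GEE. Nothing in the article says whether the GEE or the mixed model is decisive, and the two treat clustering differently. What is at stake is the width of those intervals and the error rate of those tests. The Methods wording also suggests tests over all patients and within each arm. Those are uncontrolled before/after comparisons, open to secular trend and regression to the mean whatever the clustering.

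**Working it through.** **Is there a figure of the plan's own to reproduce?** None on this point. The nearest is the 80% power under Sample size, which cannot be reproduced because the control-arm proportion is not given. It is not needed here.

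**Inputs**

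- Physicians: at least one-third of 379, so 379/3 = 126.3 (Sample size).
- Patients: the same section gives the yield, "which would capture roughly 2,500 patients with type 2 diabetes mellitus".
- Patients per physician: m = 2,500/126.3 = 19.8.
- ICC of change within physicians: not given. Assumed range 0.01 to 0.10.
- Nominal level 5%. The article does not state sidedness; two-sided is assumed.

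**Formula.** If change over time has intracluster correlation ICC within physicians, the variance of the mean change in an arm is multiplied by

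DE = 1 + (m − 1) × ICC = 1 + 18.8 × ICC.

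The same factor applies to the between-arm difference in mean change. A test that ignores it has true type I error

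2 × [1 − Φ(1.96/√DE)].

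| ICC of change (assumed) | DE | SE understated by a factor of | True type I error |
|---|---|---|---|
| 0.01 | 1.19 | 1.09 | 7.2% |
| 0.02 | 1.38 | 1.17 | 9.5% |
| 0.05 | 1.94 | 1.39 | 15.9% |
| 0.10 | 2.88 | 1.70 | 24.8% |

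**Check by simulation.** Binary before/after data were generated without any true effect for 126 physicians with 20 patients each (4,000 runs). The change in proportion was tested with a patient-level and with a physician-level variance. This is the two-time-point, identity-link analogue of the GEE.

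| Physicians differ in | ICC of change | Patient-level variance: within arm / between arms | Physician-level variance: within arm / between arms |
|---|---|---|---|
| level only (smaller spread) | 0.000 | 4.7% / 5.7% | 5.3% / 5.7% |
| level only (larger spread) | 0.000 | 4.6% / 4.8% | 5.5% / 5.2% |
| level and change | 0.016 | 9.3% / 8.1% | 5.8% / 5.0% |
| level and change | 0.039 | 13.8% / 13.3% | 5.6% / 5.3% |
| level and change | 0.074 | 20.2% / 20.7% | 5.6% / 5.4% |

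The simulation shows three things. Stable differences between physicians cancel in the within-patient change and do no harm. Once physicians differ in change, the error rises about as the formula predicts, and within-arm and between-arm tests are affected alike. Clustering at physician level brings the error back to 5.0–5.8%.

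The calculation uses patients per physician because the article does not give patients per practice. In duo and group practices the randomised cluster is larger than 19.8 patients, so at the same ICC the design effect would be larger there.

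**The case against.** The strongest reply is that the randomised comparison belongs to another model. The abstract opens with an overall multilevel rule. The Methods tie the programme effect to mixed models with a physician level, and the abstract introduces the endpoint GEE as an additional analysis. In the Methods the GEE reads as overall and within-arm evolution, whereas hypothesis one is between arms. This stands. A reader might infer that all p-values for the primary endpoints are anti-conservative; the article does not support that, because nothing makes the GEE the decisive test.

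A second reply is that inflation is not automatic. This also stands: it requires correlated change, and the article gives no value for it. Some correlation is plausible, since the intervention acts on physicians and they use the services voluntarily.

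A reader might put the sample-size ICC of 0.6 into the formula. That gives DE = 12.27, a standard error 3.5 times too small and a type I error of 57.6%. But that ICC is stated for a different outcome: a 10% improvement in any one of blood pressure, total cholesterol or HbA1c. The primary endpoints are attainment of targets, including LDL-C. The 58% is at most an extreme illustration.

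Third, the abstract does not expressly exclude physician clustering, and the article condenses a fuller plan. That tempers the point but does not remove it. The within-patient level is stated, in direct contrast to the physician level one sentence before, so this is a stated choice and not an omitted detail.

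**Conclusion.** The point holds in conditional form. As written, the endpoint GEE leaves out the randomised cluster. If change is correlated within physicians, its nominal 5% tests would run at about 7% to 25% for an ICC of change of 0.01 to 0.10, and its confidence intervals would be too narrow by a factor of 1.09 to 1.70. If physicians differ only in level, the error stays near 5%. The figures assume equal clusters of 19.8 patients, two-sided tests and a range of ICC that the documents do not supply.

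The omission does not carry over to the mixed models, which have a physician level. They do not name the practice, however, and the article does not say which method settles the primary endpoints. This should be corrected, but it does not show that the trial's main comparison is invalid.

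**What to change.** Three changes of wording in the analysis section:

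1. In the endpoint GEE, make the practice the independent cluster and use robust standard errors. Because physicians and patients are nested in practices, this also covers correlation at those levels.
2. State that the confirmatory test of hypothesis one is the between-arm (arm-by-time) contrast from one named model that accounts for the randomised practice. Either this GEE or the mixed model will do. If the mixed model is chosen, add the practice and let change over time vary between practices, because a random intercept alone absorbs only differences in level.
3. Report all-patient and within-arm before/after changes as descriptive.

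No data collection or design element changes. The cost is somewhat wider confidence intervals for the GEE results, to the extent that change really is correlated within practices.

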**Trial Registration:**

number: NTR 1369.

## Background

Diabetes management is a complex process requiring physiological, psychological, and social interventions [1,2]. Although considerable evidence supports the use of pharmacological interventions in diabetes care [3,4], the best way to improve health outcomes using non-pharmacological 'complex interventions' is often unclear [5]. A number of complex interventions target improvements in patient, provider, and organizational aspects of diabetes care [6]. The active components of these complex interventions are essential to their proper functioning and may act both independently and interdependently [7]. The Chronic Care Model (CCM) is often used as a conceptual framework to underpin complex interventions in diabetes care [8,9]. According to this model, patient outcomes such as good control of risk factors are associated with the presence of one or more interrelated components: community resources, self-management support, delivery system redesign, decision support, clinical information systems, and organizational support [8]. Most quality improvement programs in diabetes care cover several dimensions of the CCM, in particular those supported by substantial evidence of improved outcomes of care in selected populations [10]. Clinician education and dissemination of guidelines [11,12], feedback on performance [13], patient education [14,15], care management [16,17], and diabetes care teams (DCTs) to support primary care physicians [18-20] represent examples of such interventions. Few studies have applied all dimensions of the CCM to address non-adherence to evidence-based guidelines and to reduce 'clinical inertia' in primary care physicians [21-23].

Clinical inertia is defined as a lack of treatment initiation or intensification in a patient that is not achieving evidence-based goals of care [24]; this is consistent with the definition of medical errors given by the Institute of Medicine [25,26]. Clinical inertia increases the likelihood of adverse outcomes in a high proportion of patients, but it may take years for poorer clinical outcomes to become apparent [27]. Numerous authors, including those who report on clinical inertia, have defined three principal sources for non-adherence to evidence-based guidelines and clinical inertia: physician factors, patient factors, and office system and organizational factors [28-30]. Physician factors that contribute to clinical inertia include an overestimation of care actually delivered, a failure to identify and manage comorbid conditions, disagreement with evidence-based goals of care and the use of 'soft reasons' to avoid intensification of therapy (*e.g*., patient refusal) [31,32]. Patient factors that contribute to clinical inertia are limited motivation or resistance to adopting lifestyles that support optimal disease care, which stresses the importance of patient empowerment as a cornerstone to high-quality diabetes care [33,34]. Office system and organizational factors that contribute to clinical inertia are the absence of decision support and a team approach to care. These three sources interact in complex ways, and interventions to reduce clinical inertia therefore need to be multifactorial in nature. Here, we describe a study protocol of a cluster randomized trial. We have chosen the physician's practice as the unit of randomization since this was considered the most feasible method of conducting the trial. We plan to compare two different interventions for improving adherence to evidence based guidelines and reducing clinical inertia in primary care physicians.

### Aim of the study

Our program goal is to improve adherence to evidence-based guidelines and to reduce clinical inertia in primary care physicians, and to therefore improve the management of glycemic control and cardio-vascular risk factors in persons with diabetes.

### Scientific hypothesis

One hypothesis is that an advanced quality improvement program (AQIP) significantly improves clinical outcomes in persons with type 2 diabetes compared to a usual quality improvement program (UQIP). Subgroup analyses can analyze the effect of the program in the two intervention arms using cut-off values. The second hypothesis is that persons with type 2 diabetes who make use of a DCT will have significantly better outcomes compared to non-users of the DCT, regardless of their intervention arm.

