### Interventions

Two separate groups are defined: the first group will receive a usual quality improvement program (UQIP), and a second group will receive an advanced quality improvement program (AQIP). Physicians can make use of program services on a voluntary basis.

The UQIP arm will aim to improve adherence to evidence-based guidelines and to reduce the rate of clinical inertia in PCPs. The term 'usual' is applied because these interventions address the principal factors contributing to clinical inertia (physician, patient, and office system factors) and represent standard requirements for what is considered quality of diabetes care in most health care systems according to international clinical guidelines [42], and theoretical frameworks on quality of diabetes care in particular [43]. The first intervention arm is innovative to the Belgian healthcare system and adds to available insights from the international literature on how to address clinical inertia in diabetes care.

The AQIP arm will receive similar interventions, but will also include supplementary and experimental interventions that extensively focus on behavior changes in patients and providers. Interventions that focus on the patient aim at a more active involvement of the patient in his/her treatment regimen, with a special focus on lifestyle attitude changes. Improvements in 'patient empowerment' will further decrease clinical inertia by increasing the patient's willingness to intensify his/her treatment [44,45]. Interventions that target the PCP focus on improvements in communication patterns with patients, interdisciplinary shared care, and involving PCPs in community campaigns. This multi-factorial approach, with a focus on patient, provider, and organizational aspects of care, is fully in line with the latest insights and findings on high-quality chronic care, and high-quality diabetes care in particular [9,19,46-53].

The differences between the AQIP and the UQIP are outlined further below and in Table 2.

**Table 2 T2:** Overview of components of the Usual Quality Improvement Program (UQIP) and Advanced Quality Improvement Program (AQIP).

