### Level one: patient

#### Patient education/promotion of self-management

Both patients in the AQIP and UQIP arms can be referred by their PCP to a DCT to receive a medical assessment by an internist as well as to receive patient education, dietary advice, and examination by an ophthalmologist. This core membership of internists, nurse educators, dieticians, and ophthalmologists reflects the basic requirements of diabetes treatment: nutrition, medication, self-monitoring, self-management, and the management of risk factors [57]. Physicians from both the AQIP and UQIP can ask internists/diabetologists for advice on complex patient cases, with or without patient referral. Educational services and promotion of self-management to patients of the AQIP and UQIP are only provided upon referral of the physician. Nurse educators have received a post-graduate one-year training program on diabetes nursing care. The nurse educator applies individual patient counseling, didactic goal-setting, and situational problem-solving as key educational methods to patients in the AQIP, whereas patients from the UQIP receive services approximating regular care, *i.e*., individual patient counseling. Physicians from both the AQIP and UQIP can consult dieticians for complementary dietary advice or can refer their patients to discuss information on meal algorithms, dietary strategies, and tailoring food intake to meet the patients' lifestyle, motivation, and specific needs [57]. Education on lifestyle changes, identification of barriers to diabetes self-management, and stress management will be provided by a health psychologist to patients in the AQIP-program after physician referral.

Patients in the AQIP can receive additional services, including group educational sessions for both patients and relatives, education at home or at the physician's practice (provided by a traveling educator), structured and printed educational materials from the DCT and community organizations, and free tools for self-monitoring of blood glucose levels.

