### Clinician reminders

Clinician reminders for physicians of the AQIP are combined with quarterly feedback by the program manager and reminders to make use of the DCT if treatment targets are not met. Physicians are asked to remind their patients about upcoming appointments. Patients are asked by the physicians to make use of a diabetes passport in which the appointments are noted together with important treatment results. Physicians of the UQIP do not receive clinician/patient reminders nor do they receive reminders on the use of the DCT.

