### Level three: organisational

#### Team changes

Team changes are operationalized in three ways. Initially, a DCT will be installed in two primary care facilities that are run by PCPs. The DCTs will be intensively supervised by a diabetologist from the academic hospital in the project region who provides clinical leadership to the team. All DCT members will receive a 60-hour in-house training program on the use of a shared care protocol, communication skills, and team dynamics. Key elements of the interdisciplinary team include shared leadership with common goals, shared professional identity, and collaborative, rather than consultative, relationships among members [60]. Team members are expected to engage and learn from each other and to attend scheduled meetings. An experienced counselor and a member of the academic project team will oversee the training program. The DCTs operate in support of the PCPs and actively promote referrals to physicians of the AQIP if treatment targets are not met [61]. Fortnightly interdisciplinary meetings will be organized between the members of the DCT who can invite individual physicians from the AQIP to discuss complex patient conditions.

Nurse educators, dieticians, and the health psychologist will meet their colleagues from a university hospital-based diabetes team and the supervising diabetologist on a quarterly basis to exchange experiences and discuss complex patient cases. Internists will meet with the supervising diabetologist every other month to discuss individual patient cases.

Structured, extensive reports will be provided by members of the DCT to the AQIP because PCPs rank standardized, structured correspondence very high [62,63]. Physicians of the UQIP will only receive standard communication forms.

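### The second hypothesis compares diabetes care team users with non-users, a non-randomised exposure that missed targets prompt in AQIP, so the unadjusted contrast can show an effect where none exists

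*Protocol article*

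**What the plan says.** Under *Scientific hypothesis*, the protocol article follows the randomised comparison with a second hypothesis, that patients "who make use of a DCT will have significantly better outcomes compared to non-users of the DCT, regardless of their intervention arm".

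*Statistical analysis* takes this into the mixed models, which examine "whether these changes depend on patient and/or PCP's characteristics, such as the intervention program or DCT use" and refer back to hypothesis two at that point. The exposure is fixed there too: "DCT use is defined as having at least one consultation with a member of the team besides the health psychologist and the traveling educator". The stated reason for leaving those two roles out is that they serve AQIP patients only.

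Four other statements show how a patient becomes a user:

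- *Interventions*: "Physicians can make use of program services on a voluntary basis".
- *Patient education/promotion of self-management*: education and self-management services in both arms "are only provided upon referral of the physician".
- *Clinician reminders*: AQIP physicians receive "reminders to make use of the DCT if treatment targets are not met". Of UQIP physicians it says "nor do they receive reminders on the use of the DCT".
- *Team changes*: the teams "actively promote referrals to physicians of the AQIP if treatment targets are not met".

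The primary endpoints are the proportions of patients at target for HbA1c, systolic pressure and LDL-C. The secondary endpoints are mean improvements in individual parameters. The article does not call the second hypothesis observational or exploratory, and it ties no baseline adjustment to this contrast.

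**The concern.** DCT use arises after randomisation, through a physician's decision. In AQIP that decision is prompted by poor values of the variables that later serve as outcomes. Three distortions follow.

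- **Indication.** Prompted users tend to start worse, so fewer of them are likely to be at target at the end, whatever the team does.
- **Regression to the mean.** A group selected for high values falls on remeasurement. A model of change credits that fall to the team.
- **Mixing with arm.** Use is promoted only in AQIP, so users are likely to come mostly from that arm. They then also carry its quarterly feedback, extra educational sessions and logistic support. Pooling over arms credits these to the team.

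Because the trial plans both target proportions and mean improvements, the same null effect could read as harm on one outcome and benefit on the other. At stake is a published claim about the DCT that rests on selection.

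**Working it through.** The plan gives no figure for this contrast; its sample size statement concerns the two arms only. The check therefore asks what the contrast shows when the true DCT effect is zero.

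**From the document:** HbA1c target below 7%; referral linked to missed targets (AQIP); change modelled on DCT use.

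**Assumed:** HbA1c normal with mean 7.1 and SD 1.2 at both times, before/after correlation r, and referral of 50% of patients with a missed target versus 10% of the others (alternatively 40% versus 20%). Steps 1 to 4 apply the same referral rule to everyone.

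**Step 1, baseline.** z = (7.0 − 7.1)/1.2 = −0.083, so 53.3% miss the HbA1c target. The normal density at z is 0.3976. Mean if missed: 7.1 + 1.2 × 0.3976/0.5332 = 7.995. Mean if met: 7.1 − 1.2 × 0.3976/0.4668 = 6.078.

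**Step 2, users versus non-users (HbA1c-only trigger, 50%/10%).** Share of users: 0.5 × 0.5332 + 0.1 × 0.4668 = 0.313. Baseline mean of users: (0.2666 × 7.995 + 0.0467 × 6.078)/0.3133 = 7.709. Baseline mean of non-users: (0.2666 × 7.995 + 0.4201 × 6.078)/0.6867 = 6.822. Gap: 0.887. With 40%/20% the gap is 0.449.

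**Step 3, change.** The expected final value is 7.1 + r(X − 7.1), where X is baseline. The expected change is therefore −(1 − r)(X − 7.1), and the spurious difference in change is −(1 − r) × gap. At r = 0.5: −0.5 × 0.887 = −0.44. At r = 0.9: −0.1 × 0.887 = −0.09.

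**Step 4, any of three missed targets triggers referral.** Assume 35% are at the SBP target and 40% at the LDL-C target, independently of HbA1c. Both are met in 0.35 × 0.40 = 14%. A patient with HbA1c at target is then referred with probability 0.14 × 0.10 + 0.86 × 0.50 = 0.444 (or 0.14 × 0.20 + 0.86 × 0.40 = 0.372). The gaps shrink to 0.107 and 0.056.

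Each cell gives the spurious difference in HbA1c change (users minus non-users), then the percentage of users versus non-users below 7% at the end, from the bivariate normal distribution:

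| Trigger, referral | r = 0.5 | r = 0.6 | r = 0.9 |
|---|---|---|---|
| HbA1c only, 50/10 | −0.44; 36 v 52 | −0.35; 34 v 53 | −0.09; 24 v 57 |
| HbA1c only, 40/20 | −0.22; 41 v 49 | −0.18; 40 v 50 | −0.04; 35 v 52 |
| Any of three, 50/10 | −0.05; 46 v 48 | −0.04; 45 v 48 | −0.01; 45 v 49 |
| Any of three, 40/20 | −0.03; 46 v 47 | −0.02; 46 v 47 | −0.01; 45 v 47 |

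The two outcomes point in opposite directions in every cell. As r rises, the artefact in change shrinks and the gap in final attainment widens.

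**Step 5, arm.** A separate simulation assumed mean 7.2, SD 1.2, and uptake of 40%/10% (target missed/met) in AQIP and 15%/5% in UQIP. AQIP patients made up about 72% of users and 45% of non-users. If other AQIP components lower HbA1c by 0.2, the part wrongly credited to the team after adjusting for baseline but not arm is (0.72 − 0.45) × (−0.2) = −0.05. Splitting by arm without baseline adjustment does not cure the problem: at r = 0.7 and no arm effect, −0.15 remains in UQIP and −0.22 in AQIP. Adjusting for both baseline and arm brings the estimate to about zero, but only because referral in the simulation depends on nothing else.

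**The case against.** The strongest reply is that the size cannot be known and may be trivial. The text speaks of treatment targets in general, not HbA1c alone. If any missed target prompts referral, the artefact in HbA1c change is a few hundredths of a point, and a high correlation shrinks it further. This stands. No single figure should be presented as the expected bias, and a false significant result is possible, not certain.

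The missed-target prompt is also written for AQIP only. In UQIP, referral driven by poor values is a reasonable inference, not a stated rule. If UQIP referral ignored the values, the artefact would be absent within UQIP and diluted in the pooled contrast. This stands too.

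The article also names the programme as a possible model characteristic and plans a model relating evolution to initial parameters. That is a partial answer. It does not commit to arm and DCT use in one model, and the initial-parameter model is not linked to this contrast. A full covariate list may fairly be left to an analysis plan. The status of the hypothesis and the outcome modelled are stated here.

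Two stronger readings are not supported:

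- A reader might infer that DCT use will enter the between-arm model and absorb part of the AQIP effect. The wording offers the programme or DCT use and ties the latter to hypothesis two; no such joint model is specified.
- A reader might infer that AQIP patients seen only by the psychologist or traveling educator must be removed from the non-users. The definition deliberately counts only staff available in both arms. Removing those patients would be a post-randomisation exclusion in one arm, with its own selection problem.

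**Conclusion.** The concern holds on the text. The second hypothesis is a formal comparison on a non-randomised, post-randomisation exposure, and in AQIP that exposure is prompted by missing the targets that form the endpoints. Analysed as change on DCT use without baseline adjustment, it can show a difference with no true effect. The tendency is to favour users on change and disfavour them on final attainment.

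Under the assumed HbA1c distribution, the spurious difference in change runs from about 0.44 points (HbA1c-only trigger, correlation 0.5, referral 50%/10%) to about 0.01 or less (any of three targets, correlation 0.9). The document supplies no SD, correlation or uptake to place the trial within that range. The randomised comparison of AQIP with UQIP is not affected.

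**What to change.** - Label the second hypothesis exploratory and observational.
- Analyse final values, not change, adjusted for the patient's baseline HbA1c, SBP and LDL-C and for arm. Account for clustering by practice and physician, and for whether diabetes is treated by the PCP or in a diabetes clinic.
- Report the same contrast within each arm.
- Draw no causal conclusion from significance. Adjustment removes only measured confounding, and quarterly reminders mean that AQIP referral may also respond to values seen after baseline.
- Keep the current definition of use. Treating psychologist- or educator-only patients differently belongs, at most, in a sensitivity analysis.

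The cost is a change of wording and a weaker claim for this hypothesis. *Data collection* already provides for the baseline examination, the blood analysis and the PCP/diabetes-clinic indicator, so no new data are needed.
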